### Measures

#### Patient Health Questionnaire (PHQ-9)

The PHQ-9 is a self-report of frequency of symptoms for “the last 2 weeks” on each of the nine Diagnostic and Statistical Manual of Mental Disorders (DSM-IV) [33] criteria for depression, which results in a range of possible scores from 0 to 27. PHQ-9 scores of 5 – 9 represent mild depression, 10 – 14 represent moderate depression, 15 – 19 represent moderately severe depression, and >20 represent severe depression [37]. Patients with a PHQ-9 score ≥10 are considered to have clinically significant depressive symptoms. Studies in primary care samples indicate the PHQ-9 to be a reliable and valid measure of depression severity with a Cronbach’s alpha of 0.89, and has demonstrated construct validity among African American, Latino and non-Hispanic white populations [38, 39]. The PHQ-9 has been translated and validated in Spanish. The screening is designed to provide requisite information while not overburdening patients and providers. The PHQ-9 will be administered at screening prior to enrollment in the DEI, at the second session before the DEI is conducted, and one-month post-DEI. See Table 1.

#### Depression Knowledge Measure (DKM)

The DKM [40] evaluates symptom recognition and treatment knowledge. Symptom recognition is assessed with a list of 10 symptoms, including 5 DSM-IV depression symptoms and 5 non-depressive symptoms: hearing voices, sleeping too little, eating too much, being full of energy, feeling guilty, feeling agitated, being violent, loss of interest, having hallucinations, and feeling confident. Respondents receive one point for each symptom that they identify correctly as a depression symptom or not a depression symptom. Treatment knowledge is assessed with 7 true–false questions from the Griffiths et al. [41] Depression Literacy Questionnaire (D-Lit) measure, adapted for use with Hispanic populations. Respondents receive one point for each question answered correctly. With 10 symptom recognition items and 7 treatment knowledge items, the DKM scores range from 0 (all incorrect) to 17 (all correct). The measure will be administered at baseline, after the Depression Education Intervention (DEI), and one-month post-DEI session. See Table 1.

Three brief stigma measures with demonstrated validity and reliability among Spanish-speaking, Hispanic primary care patients will be used to measure key stigma constructs which deter treatment utilization [42]. The three scales will be administered at baseline, after the DEI, and one-month post-DEI, see Table 1.

#### Stigma Concerns about Mental Health Care (SCMHC)

The SCMHC [42] is a 3-item measure which assess stigma related barriers to depression treatment utilization (sample item: “I would not want to receive treatment for depression because of being embarrassed to talk about personal matters with others”). Response options are scored as 0 = “Disagree” and 1 = “Agree.” The SCMHC score is calculated by taking the sum of the 3 items and total score ranges from 0 – 3. The SCMHC has demonstrated internal consistency with a Cronbach’s alpha of .84.

#### Latino Scale for Antidepressant Stigma (LSAS)

The LSAS [42] is a 7-item measure with stigma-related statements pertaining to use of antidepressants (sample item: “Prescription medicines for depression are for people who are not strong”). Respondents indicate whether they agree with the statements on a 3-point scale ranging from 0 = “No one thinks that way” to 2 = “Everyone thinks that way.” The LSAS score is calculated by taking the sum of the 7 items and total scores range from 0–14. The LSAS has demonstrated internal consistency with a Cronbach’s alpha of .80.

#### Social Distance (SD) scale

The SD [42] is a 6-item scale, which measures desire for social distance from someone with depression or history of depression treatment (sample item: “Would you socially interact with a person who is or had been in treatment for depression if this person moves next door?”). Respondents answer no, maybe, or yes to each item, scored as 0, 1, and 2, respectively. The SD score is calculated by taking the sum of items 1 – 6. Total score ranges from 0 to 12. Lower scores indicate greater social distance. The SD has demonstrated internal consistency with a Cronbach’s alpha of .75.

### Data monitoring and analysis

The data monitoring will focus on the proper collection of the depression measures, the depression knowledge measure, the stigma measures and patient outcomes after the DEI. A Project Coordinator will be responsible for monitoring the database and provide general support to the Depression Educator concerning issues related to DESEO. Such issues might include identifying problems with implementation, support to clinical staff to insure proper use of the iPad Depression Screening and Monitoring application, and facilitate the proper recording of scores in the EHR. Other duties include maintenance and oversight of the research database, tracking of supplies of depression education materials, and ensure continued fidelity of all clinic staff to the study protocols.

A sample size of 350 would be sufficient to find a statistically significant effect size of d = .176 (α = .05, Power [1-β] = .95). While the study is expected to produce a far greater effect size, a large sample size will provide additional analytic and investigative opportunities surrounding the psychometric properties and validity of the measures. The stigma measures, in particular, have not been tested in a primary care population and are of interest in identifying barriers to mental health treatment for Hispanic populations.

The primary analysis will assess changes in knowledge of depression pre-DEI, post-DEI and one month post-DEI using the Depression Knowledge Measure and changes in cultural attitudes toward depression pre and post DEI using the stigma measures (Table 1). Additional analyses will determine if the DEI leads to engagement in depression treatment for Hispanic patients by quantifying the number of Hispanic patients diagnosed with depression who went on to begin depression treatment after the intervention. Further analysis will quantify which treatment modality the patient with depression chose after the DEI: pharmacotherapy, counseling, or other behavioral intervention based on follow-up phone call one month post intervention and/or information in the EHR.

In order to evaluate the secondary aim of feasibility of universal screening for depression utilizing the PHQ-9 [31] via the iPad Depression Screening application, a qualitative analysis will determine if the providers and other clinic staff are introducing the screening with practiced scripts and conducting warm handoffs to the Depression Educator after screening positive for depression. Additional analyses will quantify via the iPad and clinic records if all adult patients are being screened and the score is being placed in the EHR.

Other analyses of interest would determine if the iPad Depression Screening application results in changes in primary care provider approach to the diagnosis and treatment of depression. Such analyses would include comparing the number of Hispanic patients with new a depression diagnosis as a percentage of the total number of adult Hispanics patients seen in the clinic compared to a matched set the year prior to the study based on the EHR (baseline data). Additionally, quantifying changes in the number of patients with a depression diagnosis being treated with antidepressants by a primary care provider as a percentage of the total number of Hispanics patients seen in the clinic compared to a matched set the year prior to the study based on the EHR (baseline data).

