### Hypotheses

Our hypothesis is that the provision of depression education to Hispanic patients in a community based health center will lead to an increase in the understanding of depression, a reduction in stigma and an increase in patient engagement in treatment. Additionally, we hypothesize that the implementation of the iPad Depression Screening application will increase provider awareness of the incidence and prevalence of depression in their own practice and thus improve the performance and care the clinic provides.

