## Methods/Design

### Setting and participants

The study will take place at one Federally Qualified Health Center that primarily serves a Hispanic population in north Texas and whose mission is to provide a community medical home through accessible, compassionate and quality health care services. The center offers a full range of quality family-oriented comprehensive primary and preventive services, including Family Medicine, Pediatrics, Obstetrics/Gynecology, family planning services, prenatal care, and health education promotion and disease prevention services. In 2013, the clinic had 11,274 unduplicated patients and 25,362 patient visits. Of those patients, 83 % were Hispanic. The majority did not speak English.

The target enrollment for recruitment is 350 patients over the 24-month study period. All adult primary care patients at the clinic will be asked to participate in screening for depression with the iPad Depression Screening application (universal screening). The clinic sees an average of 450–500 unique adult patients per month (new and/or unduplicated) or 100–125 patients per week. It is expected that *at least* 10 % of the patient population will screen positive for depression. Patients that are not Hispanic will be ineligible for the study because the intervention is culturally and linguistically adapted for a Hispanic population. Patients who are already in treatment for depression (medication and/or psychotherapy) will also be excluded since treatment engagement is an expected outcome. The study protocol was reviewed and approved by the Institutional Review Board of the University of Texas at Arlington. All patients will provide written informed consent to participate.

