### Study design and intervention

This project will implement universal screening for depression and a Depression Education Intervention (DEI) to increase detection, diagnosis, and treatment of depression at one community health center whose patient population is majority Hispanic. The project will begin with a self-report depression screening tool that is administered to all clinic patients (universal screening) through a customized web application using an iPad. This iPad Depression Screening application technology represents an innovative, evidence-based initiative that is the first of its kind in that it aims to increase access to depression screening for patients in primary care. Through the use of the iPad Depression Screening application, patients will be identified and referred to the Depression Educator. The DEI is designed to increase disease literacy, and dispel myths about depression and its treatment. A one-group pretest-posttest design will be used to asses knowledge of depression and its treatment and related stigma before, immediately after, and one month post education intervention.

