#### Depression Education Intervention (DEI)

Patients identified as depressed by the iPad Depression Screening application (PHQ-9) will be referred to the Depression Educator for potential enrollment in the Depression Education Intervention (DEI). Patients who screen positive for depression but previously had a diagnosis of depression and are in treatment, will be excluded from enrollment in the DEI. The Depression Educator will confirm the diagnosis of major depression using the MDDC, if the provider has not already done so, and that the patient is not currently in treatment for depression or other mood disorder. The Depression Educator will explain the current project, including the compensation for completion of study measures at two sessions: baseline session to consent and enroll, and after completion of the DEI within 2 weeks. The Depression Educator will also explain that there will be one follow-up phone call one month after the completion of the DEI session. The Depression Educator will attempt to build rapport, engage the patient, and invite the patient to participate. If the patient agrees to participate in the DEI, s/he will be guided through the informed consent process. If a patient declines participation, s/he will receive routine care for their depression from the clinic providers.

The Depression Educator will document the patient’s PHQ-9 baseline score and administer the rest of the baseline measures, which includes the Depression Knowledge Measure (DKM) and three stigma measures (see Table 1). All measures will be documented in an electronic, password-protected research database. The Depression Educator will then schedule the patient to return to the clinic for the DEI. The patient will be encouraged to bring family members and loved ones to the session. The patient should be scheduled to return for the DEI within several days, at most within 2 weeks, of the first session.

**Table 1 Tab1:** DESEO study assessments and frequency of administration

Assessment	Purpose	Screening	Baseline	2^nd^ Session (pre or post DEI)	Follow-Up
Patient Health Questionnaire (PHQ-9)	Measure depressive symptoms	X		pre	X
Depression Knowledge Measure (DKM)	Evaluate symptom recognition and treatment knowledge		X	post	X
Stigma Concerns About Mental Health Care (SCMHC)	Assess stigma related barriers to depression treatment utilization		X	post	X
Latino Scale for Antidepressant Stigma (LSAS)	Assess stigma related to the use of antidepressants		X	post	X

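### The stated d = .176 at 95% power matches an undeclared one-sided paired test with all 350 enrolled patients analysed; two-sided, 350 complete pairs give d = .193, or about 91% power at d = .176

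*Protocol article*

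**What the plan says.** The power statement is in the section Data monitoring and analysis of the protocol article: "A sample size of 350 would be sufficient to find a statistically significant effect size of d = .176", with "α = .05, Power [1-β] = .95". The sentence does not say which test was assumed, whether it is one- or two-sided, or how d is standardised. The section goes on to say that a much larger effect is expected and that the large sample also serves psychometric work on the measures. It describes the primary analysis neutrally, as an assessment of changes in knowledge and attitudes.

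The number 350 also appears under Setting and participants, as a recruitment figure: "The target enrollment for recruitment is 350 patients over the 24-month study period".

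The design is a single group measured three times, the last of them a month after the education session (Study design and intervention): "A one-group pretest-posttest design will be used to asses knowledge of depression and its treatment and related stigma before, immediately after, and one month post". Patients consent and give baseline measures at a first session. The post-intervention measures need a second visit (Depression Education Intervention): "The patient should be scheduled to return for the DEI within several days, at most within 2 weeks, of the first session". The one-month measures are taken in a telephone call.

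The Hypotheses section is worded directionally: the education "will lead to an increase in the understanding of depression, a reduction in stigma and an increase in patient engagement in treatment".

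**The concern.** An alpha of .05 given without qualification is ordinarily read as two-sided. On that reading, with d as the standardised mean paired change, 350 pairs do not give 95% power at d = .176.

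The power statement also uses the enrolment target as the number analysed. A change score exists only for patients who come back for the second visit, and a one-month score only for those who are also reached by telephone. The stated sensitivity therefore needs no loss at either step. This second point does not depend on whether the test is one- or two-sided.

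What is at stake is the accuracy of a planning figure that readers will rely on when they judge how small a change the study could detect.

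**Working it through.** **Inputs.** From Data monitoring and analysis: n = 350, d = .176, alpha = .05, power = .95. From Study design and intervention: one group, before-and-after comparison. From Setting and participants: enrolment target 350. Assumed because the article does not say: d is the mean change divided by the standard deviation of the change, and loss is 10%, 20% or 30%.

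**Formulas.** For a paired t-test, power comes from the noncentral t distribution with n − 1 degrees of freedom and noncentrality d × √n. The normal approximation to the detectable effect is d = (z for alpha + z for power) / √n, with √350 = 18.708.

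**Step 1: reproduce the stated figure (one-sided).** Normal approximation: (1.645 + 1.645) / 18.708 = .1758. Exact noncentral t: d = .1762 at 95% power, and power at d = .176 is .950. The n needed for d = .176 is 350 by the normal approximation and 351 by the exact calculation. The stated figure is reproduced.

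**Step 2: the same inputs, two-sided.** Normal approximation: (1.960 + 1.645) / 18.708 = .1927. Exact noncentral t: d = .193 at 95% power, and power at d = .176 is 90.7%. To have 95% power at d = .176, 422 complete pairs would be needed (420 by the normal approximation).

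**Step 3: other forms tried.** None of these gives .176:
- Two independent groups of 175: .352 one-sided, .385 two-sided.
- Signed-rank test with relative efficiency .955: .180 one-sided, .197 two-sided.
- Repeated-measures F-test with three time points and correlation .5: 2f = .172.

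**Step 4: another route to .176.** If d were scaled by the raw-score standard deviation, it would equal the change-score d times √(2(1 − ρ)), where ρ is the pre-post correlation. The two-sided value becomes .1932 × √(2 × .415) = .176 when ρ is .585. The article states no correlation, so this route also needs an undeclared assumption.

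**Step 5: loss between enrolment and analysis** (exact noncentral t, assumed loss rates).

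| Assumed loss | Complete pairs | Two-sided d at 95% power | Two-sided power at d = .176 | One-sided d at 95% power | One-sided power at d = .176 |
|---|---|---|---|---|---|
| 0% | 350 | .193 | 90.7% | .176 | 95.0% |
| 10% | 315 | .204 | 87.6% | .186 | 93.0% |
| 20% | 280 | .216 | 83.5% | .197 | 90.2% |
| 30% | 245 | .231 | 78.3% | .211 | 86.5% |

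Even if a one-sided test was intended, the stated 95% is not reached at any of these loss rates.

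**The case against.** The strongest reply is that the figure is not miscalculated. It is correct for a one-sided paired test, the hypotheses are directional, and a condensed article may leave the test, the definition of d and a loss allowance to the full protocol. This stands in part. The arithmetic is sound under its apparent assumptions, and directional hypotheses make a one-sided planning calculation coherent. But a directional hypothesis does not declare a one-sided test. The point also does not rest on missing detail: a printed figure holds only under conditions that the article does not state.

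One-sidedness is inferred, and Step 4 shows another route to .176. That is right, and it limits how firmly the point can be put. The sentence needs clarifying on either route.

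The practical effect is small. The authors expect a much larger effect and justify 350 partly by psychometric work. As an illustration, with 245 pairs two-sided power is 97.4% at d = .25 and 99.7% at d = .30. This stands, and it settles the severity.

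A reader might go further and infer that the final tests will be one-sided, leaving no error control if stigma rises after the session. The article does not support this. A planning calculation does not fix the sidedness of the analysis, and the primary analysis is described neutrally. A one-sided test also keeps its type I error at or below .05 when the true change is adverse; what it lacks is power to declare the harm.

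**Conclusion.** The point holds as a minor to moderate one. With d read as the standardised mean paired change, d = .176 at 95% power corresponds to a one-sided test with every enrolled patient analysed, and the article declares neither condition. Two-sided with complete data, the detectable effect is .193, or power at .176 is about 91%. At an assumed 20% loss, the two-sided figures are .216 and 83.5%.

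The conclusion rests on that reading of d, on one-sidedness inferred from reproducing the figure, and on assumed loss rates. The loss argument holds for either sidedness. A reader might infer that the study is underpowered or that 350 is too few; given the effect the authors expect, the article does not support that.

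**What to change.** Keep the target of 350. Restate the power sentence as a two-sided paired comparison at alpha = .05, with d defined as the mean change divided by the standard deviation of the change. Give d = .193 at 95% power for 350 complete pairs (about 91% power at d = .176). Add the figure for the number of patients expected to have post-intervention and one-month data; for example, 280 pairs give d = .216.

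The cost is a sentence or two. No patients, visits or measures are added, and the stated figure becomes slightly less favourable. Sidedness should be settled before outcome data are analysed.

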#### Universal screening with iPad technology

The first step will involve training primary care providers and designated clinical staff in the use and interpretation of the PHQ-9 and the utilization of the iPad Depression Screening application. All adult primary care patients will be asked to complete the iPad Depression Screening (universal screening) at the annual visit and at new/non-acute visits. Using a brief script, medical assistants (MAs) will give the patient the iPad during the routine intake process (weight, blood pressure, etc.) and ask them to complete the screening for depression. Patients can refuse the depression screening process with no adverse effect to the services they receive at the clinic. The first screen in the iPad application will be used to record consent, and the patient will be informed that refusal to consent for screening will have no effect on the care they receive at the clinic. If the patient does not consent, the screening process will be terminated and the patient will continue with their scheduled visit.

The iPad Depression Screening application begins with the first two screening items of the PHQ-9 (the PHQ-2). The PHQ-2 is a validated “first-step” approach to screen for depression, which indicates if a patient should be further evaluated using the PHQ-9 [32]. For patients with scores above 3 on the first two items, the application automatically expands to the additional 7 items of the PHQ-9. The iPad Depression Screening will be presented in English or Spanish, depending on the patient’s preference. Once completed, an electronic notification is generated to the Depression Educator, the patient’s primary care provider and other designated clinic staff caring for the patient. Upon completion of the screening, the application screen will lock with a message to return the iPad to a clinic staff member.

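### The before/after EHR comparison with one matched prior year cannot support attributing changes in diagnosis and antidepressant treatment to the iPad application alone

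*Protocol article*

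**What the plan says.** The last paragraph of Data monitoring and analysis says that further analyses would "determine if the iPad Depression Screening application results in changes in primary care provider approach to the diagnosis and treatment of depression". Two outcomes are named. The first is the "number of Hispanic patients with new a depression diagnosis as a percentage of the total number of adult Hispanics patients seen in the clinic". The second is the "number of patients with a depression diagnosis being treated with antidepressants by a primary care provider as a percentage" of Hispanic patients seen. Each is "compared to a matched set the year prior to the study based on the EHR (baseline data". The matching variables are not given. No repeated time points, trend term or control clinic is named.

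The setting is a single clinic: "The study will take place at one Federally Qualified Health Center". On the rollout, the article says: "The first step will involve training primary care providers and designated clinical staff in the use and interpretation of the PHQ-9". This sentence, under Universal screening with iPad technology, goes on to cover use of the application itself. That section then brings in the Major Depression Diagnostic Checklist and the warm hand-off to the Depression Educator. Study design and intervention states the joint aim: "This project will implement universal screening for depression and a Depression Education Intervention (DEI) to increase detection, diagnosis, and treatment of depression".

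**The concern.** The question is causal and names one component, but the evidence is an uncontrolled comparison of two periods. Two things stand between that comparison and the conclusion.

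- **Calendar trend.** One prior-year percentage cannot show whether the rate was already moving. If diagnosis or prescribing was rising, the study period will be higher with no effect at all. If it was falling, a real effect will be hidden. Matching on patient characteristics does not touch this.
- **Bundling.** The application, training, checklist, warm hand-offs and DEI all belong to the same project. The antidepressant outcome is the most exposed, because the DEI is itself meant to increase engagement in treatment.

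At stake is the hypothesis that the application improves detection and clinic performance. A reader could be told that the application changed practice when drift, or the package as a whole, produced the difference.

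**Working it through.** **The plan's own figure.** The article states no figure for this comparison. Its one calculation (350 patients, d = 0.176, power 0.95) belongs to the education pre-post analysis. It reproduces as a one-sided paired test, (1.645 + 1.645)/√350 = 0.176, and has no bearing here.

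**Inputs from the article** (Setting and participants): 450-500 unique adult patients a month; 83% of clinic patients Hispanic; 24-month study period.

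**Assumptions, not in the article:** the 83% applies to adults; no patient recurs across months; base rate 3%, 5% or 10%; linear prior trend of +0.5 points a year; no effect of the rollout; a two-sided two-proportion test at 0.05; a study-side window of 12 or 24 months.

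**Step 1, yearly count.** 450 × 0.83 × 12 = 4,482 and 500 × 0.83 × 12 = 4,980.

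**Step 2, spurious difference.** The midpoints of a prior year and an adjacent 12-month window are 1.0 year apart, giving 0.5 × 1.0 = 0.50 points. For a 24-month window they are 1.5 years apart, giving 0.5 × 1.5 = 0.75 points.

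**Step 3, chance of significance.** z = (p1 − p0)/√[p̄(1 − p̄)(1/n0 + 1/n1)], and P ≈ Φ(z − 1.96) + Φ(−z − 1.96).

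Worked case, base 3%, n0 = 4,482:
- 12 months: p1 = 0.035, n1 = 4,482, p̄ = 0.0325, SE = 0.00375, z = 1.33, P = 27%.
- 24 months: p1 = 0.0375, n1 = 8,964, p̄ = 0.035, SE = 0.00336, z = 2.23, P = 61%.

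| Base rate | 12-month window | 24-month window |
|---|---|---|
| 3% | 27-29% | 61-66% |
| 5% | 19-20% | 43-47% |
| 10% | 12-13% | 27-29% |

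Each range runs from the lower to the higher yearly count. The upper 24-month value at 3% is 65% or 66%, depending on the variance used under the alternative.

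**Step 4, sensitivity.**
- Base 3%, yearly count halved by repeat visits (2,241): 16% and 35%.
- Base 3%, 24-month window, count not doubled: 50-55%.
- Base 3%, trend +0.25 points a year: 10-11% and 21-23%. Trend +1 point a year: 73-77% and about 99%.
- No trend: the usual 5%.

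**Step 5, the alternative on the same data.** Simulation of 4,000 runs: 394 patients a month (475 × 0.83), base 5%, 12 months before and 24 after, independent binomial error, one level and slope change at launch.

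| Trend per year | True step | Two-period rejection | Segmented rejection | Mean segmented step |
|---|---|---|---|---|
| 0 | 0 | 5% | 5% | 0.0 points |
| +0.5 points | 0 | 44% | 5% | 0.0 points |
| +1 point | 0 | 95% | 4% | 0.0 points |
| +1 point | 3 points | 100% | 90% | 2.99 points |

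The price is precision. With no trend, the segmented step has a standard error of 0.78 points. The two-period difference has √[0.05 × 0.95 × (1/4,728 + 1/9,456)] = 0.39 points, about half.

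**Step 6, can training be separated?** The article gives no training or launch dates. With a 3% base, 394 patients a month, 12 months before and 24 after, a training step one month before launch raises the standard error of the launch step from about 0.6 to 0.93 points. If both fall in the same month, the two steps cannot be told apart.

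**The case against.** The strongest reply has four parts.

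- **Tier.** These analyses come after the primary analysis and the secondary feasibility aim, and neither the primary conclusion nor the sample size depends on them. This stands and limits the weight of the point.
- **Unseen detail.** The article names no test or model, and a fuller plan could add one. This stands for the test. It does not stand for the comparator or the causal wording, both of which are fixed in the text.
- **Assumed magnitude.** Base rate, trend, test and window are all supplied here, and no document shows that a trend exists. This stands; hence the ranges. The article also expects at least 10% of patients to screen positive, so a true rise in diagnoses could be much larger than the drift shown. Even then the difference would belong to the package.
- **Training.** A reader might infer that training is a rival cause wrongly credited to the application. The documents do not support that. The training covers use of the application as well as the PHQ-9, and sits under the screening heading, so it is part of the rollout. The clearer co-interventions are the DEI, the checklist and the warm hand-offs.

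A reader might also infer that the EHR is known to supply monthly series. The article does not say so. It is a reasonable expectation from dated records and has to be confirmed.

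**Conclusion.** The concern holds, with moderate weight. A matched set from one prior year at one clinic cannot separate the rollout from a calendar trend, and nothing in the comparison separates the application from what was introduced alongside it. The result can support a before/after association for the package, but not an effect of the application alone.

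Under the stated assumptions with a trend of +0.5 points a year, a null rollout would look significant in about 12-29% of cases (12-month window) or 27-66% (24-month window), and less often with repeat patients. These figures show what the design cannot exclude; they do not predict this clinic's result. It would be too strong to say that the study's main findings on knowledge and stigma are affected.

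**What to change.** 1. Confirm that dated EHR records allow it. Then extract monthly numerators and denominators for adult Hispanic patients seen, for at least 12 and preferably 24 months before rollout and through the study.
2. Fit a segmented model with a pre-existing slope and one level and slope change at rollout, with standard errors robust to autocorrelation. Report these changes in place of the two-period difference.
3. Record the training and launch dates. Add a separate training step only if they are far enough apart to estimate it.
4. Word the result as the effect of the whole package (training, application, checklist, warm hand-off, DEI), not of the application alone.

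The cost is a longer EHR query, one model and wider intervals: about twice the standard error in the 5% base-rate example with 12 months before rollout. No patient procedure changes.
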